### Sample Size Estimation

To evaluate the effect of the intervention, that is lithium carbonate on improvement of rates of AKI, we will consider rates of AKI in cardiac surgery patients to be about 20% based on prior data (44, 45). A 25% reduction of this rate is considered clinically significant. Cocks and Torgers (46) proposed a sample size calculation for pilot randomized trials based on confidence interval in which the lower limit of one-sided confidence interval (CI) is greater than the clinically significant effect size in order to exclude the estimate that is considered clinically important. Based on the CI approach, a sample size of 182 with 91 in each group is required to produce a one-sided 80% confidence limit that would exclude a 5% difference. The one-sided confidence interval method is being used since we are only interested in proceeding toward a larger trial if there is evidence of efficacy. Because this is a control vs. intervention study design, there is an inherent improvement in the confidence limit since the controls will constrain some of the random error. This sample size agrees with the recommendation of Teare et al. (47), who suggested 60–100 subjects to estimate the event rate in an intervention group and ensures that we will encounter at least one incident at a 99% confidence level (48). Accordingly, a minimum sample size of 58 with 29 in each group is enough to ensure that at least one event would be detected and is a measure of feasibility that the study can detect the clinically significant outcome.

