### Randomization

This will be done by pharmacy according to block technique in 1:1 ratio to either lithium or placebo. Subjects and health care providers will be blinded to the allocation.

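### The minimum of 58 patients is sized to see at least one AKI event per arm; it does not support detecting the clinically significant 5-point reduction, for which the protocol's own criterion needs 182

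*Protocol article*

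**What the plan says.** All the sizing statements stand in the protocol article, Sample Size Estimation.

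- Planning rate: "we will consider rates of AKI in cardiac surgery patients to be about 20% based on prior data".
- Effect of interest: "A 25% reduction of this rate is considered clinically significant". On a 20% base this is 20% to 15%, or 5 points.
- Required size: "a sample size of 182 with 91 in each group is required to produce a one-sided 80% confidence limit that would exclude a 5% difference".
- On the role of the control arm: "there is an inherent improvement in the confidence limit since the controls will constrain some of the random error".
- On event capture: the sample "ensures that we will encounter at least one incident at a 99% confidence level".
- Closing sentence: "a minimum sample size of 58 with 29 in each group is enough to ensure that at least one event would be detected", and this "is a measure of feasibility that the study can detect the clinically significant outcome".

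The Randomization section sets allocation "according to block technique in 1:1 ratio to either lithium or placebo". The Statistical Analysis section names a chi-square test of the AKI proportions as the primary analysis, with significance at p < 0.05 and a one-directional alternative.

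**The concern.** One paragraph offers a required size and a minimum size that is enough. They differ about threefold (182/58 = 3.1), and nothing says which governs. The smaller number rests on seeing at least one AKI case, yet the sentence that introduces it ends with a claim about detecting the clinically significant outcome. Earlier in the section that adjective belongs to the 25% reduction. Seeing at least one case tells the reader that events occur; it does not tell them whether two arms differ by 5 points.

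The stake is how a small trial could be described. The same section makes a larger trial conditional on evidence of efficacy, and the Discussion makes it conditional on a significant difference. If recruitment ended near 58, the closing sentence could be cited to say that an adequate size had been reached.

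The sentence on controls adds to this by suggesting that the real precision is better than the calculation shows.

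**Working it through.** **Inputs.** Control rate 20%, effect 5 points (20% to 15%), one-sided 80% limit, 91 and 29 per arm, and 99% for at least one event, all from Sample Size Estimation; 1:1 allocation from Randomization; chi-square test at 0.05 from Statistical Analysis. z(0.80) = 0.8416. The 15% rate in step 2 is inferred, because the protocol does not say which rate it used there.

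**1. Reproduce 182.** n per arm = [p1(1−p1) + p2(1−p2)] × (z/0.05)². With 20% in both arms (observed difference zero): 0.32 × (0.8416/0.05)² = 90.7, so 91 per arm and 182 in total. This matches. With 20% and 15% the same formula gives 81.5, so 82 per arm, which does not match. The 182 therefore assumes 20% in both arms, and it already contains the variance of both arms.

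**2. Reproduce 58.** n = ln(0.01)/ln(1−p). At p = 0.15: 28.3, so 29 per arm and 58 in total. This matches. At p = 0.20: 20.6, so 21. With 29 patients the chance of at least one event is 1 − 0.85^29 = 99.1% at 15% and 1 − 0.80^29 = 99.8% at 20%. Expected events are 29 × 0.20 + 29 × 0.15 = 5.8 + 4.35, about 10 in total.

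**3. Apply the protocol's own precision criterion to both sizes.** Half-width = z × √{[p1(1−p1) + p2(1−p2)]/n}.

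| Per arm | 20% and 20% | 20% and 15% |
|---|---|---|
| 29 | 0.8416 × √(0.32/29) = 8.8 points | 0.8416 × √(0.2875/29) = 8.4 points |
| 91 | 0.8416 × √(0.32/91) = 4.99 points | 0.8416 × √(0.2875/91) = 4.7 points |

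At 29 per arm an observed difference of zero leaves a 5-point benefit inside the limit. With the 8.8-point half-width, the observed result would have to favour placebo by more than 8.8 − 5 = 3.8 points to exclude it.

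**4. Power of the planned chi-square test for 20% versus 15%.** This was found by summing the binomial probabilities of all tables that reach significance (no continuity correction).

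| Per arm | Two-sided 0.05 | One-sided 0.05 |
|---|---|---|
| 29 | 7.8% (7.0% in lithium's favour, 0.7% in placebo's) | 13% |
| 91 | 14% | 22% |

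**5. The sentence on controls.** The variance of a difference is the sum of the two arms' variances. Step 1 shows that this sum is what produces 91 per arm. The primary comparison is an unadjusted contingency table, so there is no pairing or covariate adjustment from which a further gain in precision could come.

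**The case against.** The strongest defence is that the protocol never says 58 patients are enough for the efficacy comparison. It ties 58 to capturing an event and calls that a measure of feasibility, while the confidence-limit criterion is tied to 182. On this view, outcome means an AKI case: the Abstract uses that word for AKI incidence, and the section elsewhere speaks of an effect size or a difference when it means the treatment effect. This reading is possible, and it limits the point to one of wording and consistency. It does not remove it, because the section applies the term clinically significant to the 25% reduction, so the closing clause naturally reads as a claim about that reduction.

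Some stronger readings are tempting and are not supported:

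- That 58 is miscalculated. It is not; both sizes reproduce.
- That 58 patients would yield little more than one event. About 10 are expected.
- That 58 can never exclude a 5-point benefit. It could, if the observed result favoured placebo by more than about 3.8 points.
- That low power singles out 58. It does not: power at 182 is also low, and the section makes no power claim for either size.
- That the trial plans to stop at 58 and conclude on efficacy. No such rule is stated.

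The sentence on controls could also be meant as a remark that concurrent controls avoid the extra uncertainty of a historical comparison. That is a fair argument for having a control arm, but it gives no improvement over the limit already calculated for two arms.

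**Conclusion.** The point holds as a fault of inference and consistency. The two sizes answer different questions, and the one called a minimum lacks the property that the section requires: its one-sided 80% half-width is 8.8 points (8.4 at 20% versus 15%), against 4.99 at 91 per arm. The clause about detecting the clinically significant outcome is unsupported if it refers to the 5-point reduction, and unclear if it refers to an AKI case. The claimed extra gain from controls is unsupported on either reading.

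These figures rest on the protocol's 20% rate, a normal-approximation limit, and the inferred 15% for the 29. A reader might infer that restoring 182 makes the chi-square test adequate. It does not: at about 14% two-sided or 22% one-sided power, 182 meets the pilot confidence-limit criterion and nothing more.

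**What to change.** In Sample Size Estimation:

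1. State 182 (91 per arm) as the single target, and say that it is set by the confidence-limit criterion and not by the power of the chi-square test.
2. Delete the 58. If it is kept, call it a floor for event capture, state the event rate assumed, give its 8.8-point half-width, and say that no efficacy or progression conclusion will be drawn from that number.
3. Delete the clause on detecting the clinically significant outcome.
4. Delete the sentence on controls improving the confidence limit.

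The cost is wording only. Neither the target of 182 nor the conduct of the trial changes; the fallback claim becomes less favourable.

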## Discussion

AKI is a devastating complication that can develop after cardiac surgery, it dictates patient outcomes and impacts morbidity and mortality. It has been shown in a number of studies that AKI independently increases the length of hospitalization, impacts utilization of resources and worsens mortality up to 10 years after surgery (14, 49, 50). Patients who develop CSA-AKI are also at increased risk for developing CKD (51). Prior to using RIFLE and AKIN criteria, the definition of AKI was not standardized and hence incidence of AKI has been variable. Based on AKIN and RIFLE stage 2 criteria the reported rates of AKI after cardiac surgery are 4 to 9% (52–54), although according to stage 1 the incidence rises up to 20% (54, 55).

The pathogenesis of AKI during cardiac surgery is complex and likely multifactorial. Since renal biopsies are rarely done unless injury is felt to be secondary to glomerulonephritis, the histopathological studies are limited. Factors relevant to the development of AKI include patient factors such as advanced age, gender, prior heart failure, baseline CKD, chronic obstructive pulmonary disease or diabetes mellitus (22, 56, 57), procedure-related factors such as duration of surgery, duration of CPB, aortic cross clamp time, exogenous vasopressor use, hemodilution, hypothermia, embolism, and duration of surgery (5, 58–60). Moreover valvular surgery, combined surgery and emergency surgery carry a higher risk for AKI (5). Exogenous factors such as medications like non-steroidal anti-inflammatory agents (NSAIDs), diuretics renin angiotensin system blockers (RAS blockers), and radiocontrast could also impair glomerular autoregulation (61, 62). Moreover, genetic predisposition is important too with apolipoprotein epsilon 4 allele being protective while 2 and 3 increase risk of AKI (5, 63). Furthermore, endogenous toxins such as heme or iron also play an important role. Many patients experience perioperative hypoxia that can lead to endothelial injury by various cytokines (64, 65). During manipulation of aorta and cross clamping there is risk of embolization of gas, debris and atherosclerotic plaque (66, 67). Besides, CPB results in systemic inflammatory immune response due to contact between blood and artificial surface of the CBP circuit. This can lead to release of various cytokines and free radicals (68, 69). The renal medulla is especially sensitive to free radical damage as it lives in a state of perpetual hypoxia (70). All these factors lead to AKI in susceptible patients.

Many efforts have been made to try to mitigate CSA-AKI. For instance, a small prospective study was done to evaluate beneficial effect of thoracic epidural anesthesia compared to general anesthesia leading to slightly reduced incidence of AKI (2 vs. 6.9%) (71). Remote ischemic preconditioning (RIPC) is thought to have a protective effect on distant organs *via* immunomodulation, humoral and neurogenic pathways. It has been shown in meta-analysis that there is a trend for reduction of AKI by using RIPC (72). Besides, an intra-aortic filter has been used to reduce risk of embolization. These atheroma filtration machines have not been able to prevent AKI but have led to improved cognition post-coronary artery bypass grafting surgery (73). In addition, diuretics have been tried for preventing AKI but have shown to worsen the disease (74, 75). In smaller studies, fenoldopam seemed to show some promise. It activates adenylate cyclase and inhibits sodium-potassium ATPasa leading to vasodilation and natriuresis in the proximal tubule and loop of henle. However, a large randomized controlled trial showed no difference in renal replacement therapy and trial was stopped early due to futility (76). In another small study, atrial natriuretic peptide showed reduced risk of renal replacement therapy at 21 days after cardiac surgery. However it causes hypotension (77, 78). Prophylactic hemodialysis has also been tried by Durmaz et al. but it was found to increase morbidity and mortality (79). The mainstay for CSA-AKI is really prevention and supportive therapy. Hence, there remains an opportunity for developing novel therapeutics to prevent or treat CSA-AKI.

Failure of clinical trials of new therapies for CSA-AKI is due, at least in part, to lack of a sensitive and specific marker for AKI. SCr is not a reliable marker for AKI. It is influenced by muscles mass, protein intake, volume status. Urine output also depends on confounding factors such as diuretics use, fluid administration and others. Hence, it is plausible that if we rely only on urine output or SCr we may miss some patients with relatively more short lived AKI, fluctuating volume status or low muscle mass. Some new biomarkers have been characterized in CSA-AKI and have shown to be helpful in the detection of early AKI (80). Urine TIMP-2 and IGFBP7 are new biomarkers for AKI and perform better than existing markers. They are both inducers of G1 cell-cycle arrest. In a study of 42 patients undergoing cardiac surgery, 38% developed AKI. Urinary [TIMP-2]·[IGFBP7] was found to be a sensitive and specific marker of AKI after cardiac surgery (81). In another study of patients undergoing CPB surgery the urinary [TIMP-2]·[IGFBP7] ratio was not able to detect AKI in the early postoperative period but did identify AKI patients on the first post-operative day (82). Based on existing evidence, we will also apply the NephroCheck test, an FDA-approved immunoassay test that measures the urinary concentrations of [TIMP-2] × [IGFBP-7], and measure urinary [TIMP-2]·[IGFBP7] on post-operative day 0, 1 and 2.

Recently, more and more data suggest that GSK3β plays a detrimental role in the pathogenesis of AKI in animal models exposed to nephrotoxic substance or subjected to renal ischemia/reperfusion injury or endotoxemia. Therapeutic targeting of GSK3β by genetic knockout or various selective chemical inhibitors has a demonstrable benefit in a number of pre-clinical studies of AKI. The underlying mechanism has been attributed to mitigated renal tubular cell apoptosis, diminished renal inflammation, boosted antioxidant response, and enhanced renal tubular repair. Among the many selective inhibitors of GSK3β, lithium is of particular interest because it has been safely used in patients with mental diseases as a FDA-approved mood stabilizer for over 50 years (83). However, in order to achieve an actionable concentration in the brain, the ionized lithium needs very high dose to pass through the blood-brain barrier, and produce therapeutic effects in psychiatric disorders. At the high psychiatric dose of lithium for long term, some adverse effects can be elicited in peripheral organs including the kidney. While the exact “kidney-protective dose” of lithium is still unknown, latest evidence from animal data suggests that a small dose of lithium for short term unequivocally exerts a potent renoprotective effect in multiple pre-clinical models of AKI, including nephrotoxic AKI, septic AKI and ischemic AKI (36). Even a delayed treatment with microdose lithium could successfully protect against AKI and promote kidney repair and recovery of kidney function (35). All existing evidence infers that short term microdose lithium therapy may be repurposed for preventing AKI.

In summary, opportunities exist in the field of AKI for newer, efficacious therapies. It is promising that low dose lithium has potential to promote tubular regeneration and hence may ameliorate AKI due to acute tubular necrosis in the setting of cardiac surgery. Successful completion of this pilot study will help to assess the effectiveness of lithium in CSA-AKI. If we find a significant difference in the intervention group, this will pave the way for large full scale randomized trials to further evaluate the potential of this novel regimen.

## Abbreviations

AKI: acute kidney injury
AKIN: acute kidney injury network
CKD: chronic kidney disease
CKD-EPI: chronic kidney disease epidemiology collaboration
CPB: cardiopulmonary bypass
CSA-AKI: cardiac surgery associated acute kidney injury
SCr: serum creatinine
CI: confidence interval
eGFR: estimated glomerular filtration rate
FDA: food and drug administration
GSK3β: glycogen synthase kinase
LiCS-AKI: lithium in cardiac surgery-associated acute kidney injury
RRT: renal replacement therapy
TIMP-2: tissue inhibitor of metalloproteinases-2
IGFBP7: insulin-like growth factor-binding protein 7
ROC: receiver operating characteristic
RIPC: remote ischemic preconditioning.
